## Abstract

**Background:**

In the Netherlands, more than half of the teachers working in primary education experience high levels of work stress. Compared to other professions, teachers are more likely to drop out from work and develop mental illnesses. Almost one in five even choose a new profession within 5 years after starting as a teacher. This indicates an urgent need for interventions to reduce stress levels in teachers. However, few evidence-based effective interventions targeting stress and work-related problems in the primary educational system are available.

**Aim:**

In the current paper, we describe the protocol for a randomized controlled study (RCT) comparing an 8-week mindfulness-based stress reduction (MBSR) intervention with a wait list control condition in primary school teachers. We hypothesize that teachers who participate in the MBSR programme will report less stress (primary outcome) than those in the control group at post-test and at 3-month follow-up. We also expect a decrease in teachers’ absenteeism and improvements of mental health, teacher skills, classroom climate quality and the pupil-teacher relationship (secondary outcomes). Finally, we hypothesize that self-compassion, mindfulness skills and emotion regulation skills could mediate effects.

**Methods/design:**

A mixed-method study will be conducted among *N*=155 Dutch primary school teachers (grade 1 to 6). The quantitative study will be an RCT, in which teachers will be randomly allocated to the MBSR or waiting list control condition. Trial participants will not be made actively aware of their condition. The data analysts will be blinded. Online questionnaires will be sent to teachers before and after the MBSR programme, and at 3-month follow-up. Information about absenteeism will be collected. In the qualitative part of the study, we will interview teachers to examine their perceived effects of MBSR on their teaching skills, the classroom climate quality and the pupil-teacher relationship.

**Discussion:**

This protocol paper describes a mixed-method study design with an RCT and a qualitative evaluation to evaluate an MBSR programme on perceived stress among primary school teachers. If the MBSR programme proves to be effective, it could be implemented as a programme to reduce stress and improve mental health and teaching outcomes in primary school teachers.

**Trial registration:**

Nederland Trial Register NL. Registered on 19 November 2019—retrospectively registered, https://www.trialregister.nl/trial/8171

## Background

In recent years, teachers in primary education report increasing levels of work pressure. For more than half of the teachers (i.e. 56%) in the Netherlands, this work pressure is unacceptably high [1]. This pressure is not only related to the quantity of work, but also to the emotional demands of the work [2]. According to the Transactional Model of Stress and Coping (Lazarus, 1991 [3];), experienced stress is the result of the interpretation of a stressor and the capacity to regulate emotions. The continued experience of negative emotions in reaction to external stressors can cause feelings of stress [4]. Continuing high levels of stress can, in turn, lead to absenteeism or premature outflow from the profession in which the stress is experienced. In the Netherlands this is reflected in a high percentage of absenteeism and burnout symptoms in primary school teachers [5]. Furthermore, figures show that of all starting teachers, one in five leave the Dutch educational system within 5 years. One in eight teachers is actively searching for employment outside the educational field. Work pressure and related stress are specified as the most important reason [6].

Continued stress in teachers leads to adverse effects on their mental health and well-being. Roffey [4] conducted research in six Australian schools and showed that the extent to which teachers can cope with stress and regulate their emotions influences both cognitive and social performances. Stress and coping with stress also affect so-called teacher skills: skills needed to be capable of delivering high-quality education and establishing effective class management [7]. A review by Spilt et al. [8], in which results of 99 studies have been analysed, showed that stress in teachers had a negative impact on the pupil-teacher relationship. In turn, a poor pupil-teacher relationship had both direct and indirect adverse effects on the teacher’s mental health and wellbeing [3, 9]. It also led to misbehaviour, lack of motivation and diminishing achievements in pupils [3, 4, 8], which may also contribute to perceived teachers’ stress [2].

Even though there seems a great need for alleviating stress in teachers, studies exploring ways to do so in primary schools are limited [2]. A meta-analysis of 65 independent studies on teachers’ stress showed that improved emotion regulation could be the key to stress reduction [2]. Only 17 of these studies concerned primary school teachers. However, research shows that primary school teachers are emotionally more involved in their teaching than teachers in higher education [10]. Unlike teachers in higher education, primary school teachers teach their pupils for 5 days a week. Skills such as insight into their own emotions and thoughts and the capacity to regulate these effectively while teaching, might contribute to reduction of perceived stress. Teachers who possess these skills are able to build supporting relationships with their pupils more effectively, experience more positive emotions, possess more mental resilience and experience more job satisfaction [2].

Besides the influence of teachers’ experienced stress on their own well-being and functioning as a teacher, this stress may ultimately affect their pupils as well [11]. Briner and Dewberry (2007) have found indications that the level of well-being of the teacher affected the classroom climate. A physically and socially safe classroom climate is a necessary condition for pupils to be able to learn, and classroom climate directly affects the well-being and performance of pupils [3, 12–14]. In addition to the development of didactic and organizational qualities, the development of a good pedagogical relationship with pupils is therefore of great importance [4]. Providing teachers with means to alleviate stress and improve their mental health and well-being is thus not only in the interest of teachers themselves, but also in the interest of their pupils.

### Mindfulness-based stress reduction (MBSR)

A promising method to improve emotion regulation and reduce stress symptoms is mindfulness-based stress reduction (MBSR) as developed by Jon Kabat-Zinn (2004). Kabat-Zinn defines mindfulness as ‘Being aware in a special way: be consciously present in the here and now, without judgment’. Mindfulness can contribute to reducing stress by gaining insight in behavioural patterns, creating emotional awareness, and develop regulation of emotions [15].

A meta-analysis of 29 studies on effectiveness of mindfulness interventions in healthy adults showed a reduction of experienced stress, depressive and anxiety symptoms and improvements of quality of life [16]. The results of a review and meta-analysis including over 12,000 people with psychiatric disorders such as depression demonstrated that mindfulness-based interventions were as effective as other evidence-based treatments including cognitive behavioural therapy and anti-depressant medication [17]. An article by Tang et al. [15] specifically confirmed the positive effect on the regulation of emotions. Other studies showed promising effects of MBSR on worrying, regulation of attention and emotions, personal achievements and empathy [7].

Although there are promising effects of mindfulness on stress and mental health in diverse populations, only few studies have been conducted to date on the effectiveness of mindfulness in primary school teachers. Most of these studies have been conducted in the USA. European studies are generally lacking, and no studies on this subject have been conducted in the Netherlands.

Jennings and colleagues’ research (2017) in 224 American K-5 grade teachers is the largest RCT to date that examines the effectiveness of a mindfulness-based intervention (MBI) for teachers in primary education. In contrast to the control group, the intervention group displayed significant reduction of stress and perceived time pressure. In addition, teachers in the intervention group reported an improvement of mental health and well-being. They experienced more self-awareness, mindfulness (i.e. observing without judgement) and better regulation of emotions. They reported to be able to deal with their pupils’ behaviour more effectively and more compassionately. This is reflected in the fact that 91% of the teachers in Jennings’ study reported to be more capable of starting and maintaining a supporting relationship with their pupils. The study by Jennings and colleagues delivers the most compelling evidence so far that MBIs can contribute positively to stress experience, mental health, executive functions, teacher skills, the classroom climate and the pupil-teacher relationship in primary school teachers.

Earlier studies in teachers from various forms of education [18–20] showed that when teachers can deploy mindfulness skills, they were more capable of assessing emotionally provoking situations in the classroom and reacting adequately. This resulted in less stress and more mental well-being. This way, mindfulness skills positively affected the interaction with pupils and the pupil-teacher relationship.

Because of the lack of studies outside the USA, we conducted an uncontrolled pilot study to examine the potential of an MBSR programme within 71 primary school teachers. After the training, participants showed a significant reduction of perceived stress (PSS, Perceived Stress Scale) and improvements of psychological, emotional and social well-being (MHC-SF, Mental Health Continuum-Short Form). In addition, the pilot study showed a significant increase in both mindfulness skills (FFMQ-SF, The Five Facet Mindfulness Questionnaire Short Form) as well as self-compassion (SCS-SF, Self-Compassion Scale-short Form), both of which are related to mental health. In addition, we tested several potential moderators and found indications for possible moderating effects of school weight and current or past psychological problems on the impact of the MBSR programme. Because of these promising results we will test the effectiveness of MBSR in Dutch primary care teachers on larger scale including a control group by conducting an RCT.

### Aims of the trial

The primary aim of this study is to investigate the effectiveness of MBSR in contrast to a wait list control condition in reducing perceived stress in teachers in primary education. The secondary aim is to examine the effects of the MBSR on (a) absenteeism of teachers, (b) teachers’ mental health, (c) teacher skills and (d) teachers’ experienced classroom climate and pupil-teacher relationship.

The third aim is to examine possible mediating factors of treatment outcome, such as mindfulness skills (i.e. observing, describing, acting with awareness, non-judgement and non-reactivity), self-compassion and emotion regulation skills. Based on research by Jennings [2], Roeser [18], Roeser et al. [19] and Skinner and Beers [20], we hypothesize that an improvement of mindfulness skills, self-compassion and emotion regulation skills will lead to a reduction of perceived stress. In addition, we explore whether school weight, age, past and present psychological problems and teachers’ years of experience act as potential moderators of programme effects. The final aim is to conduct qualitative interviews after the MBSR programme to get a more in-depth view of teachers’ perception of the impact of MBSR on their teacher skills, classroom climate and pupil-teacher relationship.

## Methods/design

### Study design

The design of the study is a superiority RCT in which primary education teachers are randomly allocated with a ratio of 1:1to either the MBSR programme or the waiting list control condition (see Fig. 1). Because of practical and financial constraints, the control condition consists of no intervention. As we would like to offer MBSR to all the teachers who express interest, we also wanted to be able to offer it to those allocated to the control condition. The study protocol has been ethically approved by the Internal Review Board (IRB) of the [masked for blind review] and is registered under number ECSW-2019-029.

**Fig. 1 Fig1:**
[figure not shown]
Flow diagram of the study design

### Participant characteristics

The study population will consist of Dutch teachers in primary education teaching groups 1–8, comparable to grades 1 to 6 in the US school system.

#### Eligibility criteria

We will include teachers who meet the following criteria: (a) teaching at least two days in the same group during a school year between the start of the school year and March, (b) willing to fill out questionnaires in Dutch three times in a school year and (c) able to start the programme in either September or March.

Exclusion criteria will be previous participation in a Mindfulness-Based Cognitive Therapy, MBSR programme or a mindfulness-based workshop of more than 3-h duration. During the trial, there will be no restrictions with regard to concomitant interventions. However, participants will be requested to not participate in an MBSR course offered elsewhere if they are allocated to the wait list control condition.

### Procedure and allocation

Recruitment will take place in a large urban area in the Netherlands. School boards in the study area will be informed about the study and asked to make their teachers aware of it. Teachers will also be recruited by social media and by presentations at schools. Interested teachers will receive an information leaflet and be invited for a screening interview by telephone. Teachers who are willing to participate will provide written informed consent which will be obtained by one of the researchers ([name]).

Participants will receive online questionnaires, which will be processed anonymously. Questionnaires will be administered before and after the MBSR or wait list period (September and November), and at 3 months’ follow-up (March). As participants will be aware whether they have or have not participated in the course by the time they complete the follow-up assessments, they cannot be kept completely blinded. We will compare data related to teacher absenteeism from the school year prior to that in which they participate in the research. After completion of the follow-up, teachers of the control group will be offered the MBSR programme as well. To include the required 155 participants, the intervention procedure between September and June will be repeated for three consecutive school years.

The Ethics Committee Social Science (Radboud University) agreed (ECSW-2019-029) that there was no risk of physical or mental harm for participants during this trial. The Faculty of Social Science takes the juridical responsibility for accidents and damage caused by participating in the research. If participants report any adverse events during the trial, either during the MBSR course or during the wait list control condition, this will be registered in the electronic database system Castor. In case of serious adverse events, these will be reported to the Ethics Committee. If participants require additional mental health support, they will be referred to the regular services, but it is also possible for participants to consult with an appointed psychologist if they so request, or if the trainer so advises. This psychologist collaborates with the overarching school organization/foundation to which most of the participating schools and therefore teachers in this study belong. If recruited participants do not attend the MBSR course, they will be contacted by the MBSR teacher. If they decide to discontinue, they will be given suggestions on how to obtain mental health support if needed. Lastly, if participants have questions about the study or the planning, they can always contact one of the researchers whose contact details are listed in the consent letter. These details also include the contact details of an independent supervisor at the Radboud University who can be contacted in case of complaints.

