### Intervention

The intervention will consist of the MBSR training developed by Kabat-Zinn [22] which consists of 8 weekly group (6–15 persons) sessions with a duration of 120 min each. In the 6th week, an additional session of practice in silence with a duration of 6 h will be included. The intervention consists of three primary components: (1) formal and informal meditation exercises, such as sitting meditation and yoga, (2) dialogue and (3) psychoeducation about stress and stress responses. A folder will be provided with information about each week’s session. Participants will be asked to practice daily for at least 35 min.

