### Mindfulness teacher

The MBSR will be given by a mindfulness teacher who meets the criteria of the Association of Mindfulness Based Teachers in the Netherlands and Flanders and the internationally agreed good practice guidelines of the UK network for Mindfulness-Based Teachers mindfulnessteachersuk.org, 2015). If the trainer notes that a participant might be in need of additional mental support or if a participant indicates this him- or herself, a licensed psychologist is available who can be contacted during as well as after the programme.

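### Adverse events are registered when participants report them, but only the MBSR arm has regular trainer contact, so any event counts by arm would be prone to unequal ascertainment

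*Protocol article*

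**What the plan says.** All references are to the protocol article.

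- **Trigger for recording (Procedure and allocation).** Registration in the data-capture system starts from a report: "If participants report any adverse events during the trial, either during the MBSR course or during the wait list control condition". The wording is the same for both arms.
- **Serious events (same section).** "In case of serious adverse events, these will be reported to the Ethics Committee". No separate way of detecting them is given.
- **Contact under MBSR (Intervention).** The course has "8 weekly group (6–15 persons) sessions with a duration of 120 min each", plus one 6-hour session in week 6.
- **Contact on the wait list (Study design).** Here "the control condition consists of no intervention".
- **Routes through the trainer.** Under Mindfulness teacher, a psychologist is available "If the trainer notes that a participant might be in need of additional mental support" or if the participant says so. Under Procedure and allocation, participants may "consult with an appointed psychologist if they so request, or if the trainer so advises". The same section adds: "If recruited participants do not attend the MBSR course, they will be contacted by the MBSR teacher".
- **Routes open to both arms.** There are questionnaires in September, November and March, reminders and then a telephone call for non-response, a note of the reason for discontinuing, the researchers' contact details, an independent supervisor for complaints, and the psychologist on the participant's own request.
- **Schedule (Table 1).** It lists outcomes and mediators. Adverse events are not among them.

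**The concern.** A rule worded identically for two arms does not give equal recording if one arm has far more occasions on which an event can come up. In this trial the gap follows from the design: a course with a trainer against no intervention.

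Two things are at stake. First, a reader who sees event counts by arm in the trial report cannot tell an effect of the course from an effect of contact. Second, an event that the questionnaires do not measure, or that arises and settles between them, depends on the teacher coming forward. On the wait list there is no regular meeting at which that might happen. Serious events depend on the same reporting step, since the article gives no other way of learning of them.

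An analysis plan cannot repair this later, because events that were never collected cannot be analysed.

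**Working it through.** The article gives no adverse-event rate and no detection probability, so there is no stated figure to reproduce. The check has three parts.

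**1. Scheduled contact between baseline and post-test**

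- MBSR: 8 sessions × 2 h + 1 session × 6 h = 16 + 6 = 22 h, in 9 meetings.
- Wait list: 0 h, in 0 meetings.

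**2. Routes by which an event could come to notice before follow-up ends**

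| Route | MBSR | Wait list |
|---|---|---|
| Group sessions with trainer | 9 | 0 |
| Trainer notes a need, or advises the psychologist | yes | no trainer |
| Trainer contacts non-attenders | yes | not applicable |
| Questionnaires in September, November and March | yes | yes |
| Call for non-response; reason for discontinuing noted | yes | yes |
| Own approach to researchers, supervisor or psychologist | yes | yes |

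The first three rows exist in one arm only. The last three are shared, but the article puts no adverse-event question in any of them.

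**3. What unequal capture could do (illustration only; risks and capture probabilities are assumed)**

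Let p1 and p0 be the true risks under MBSR and on the wait list, and s1 and s0 the probabilities that an event is recorded. The recorded rates are p1·s1 and p0·s0. If p1 = p0, the recorded ratio is s1/s0, whatever the true risk. With 155 participants allocated 1:1, each arm has about 155/2 = 77.5.

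| True risk, MBSR / wait list | Capture, MBSR / wait list | Recorded rates | Expected counts | Ratio |
|---|---|---|---|---|
| 10% / 10% | 90% / 90% | 9% / 9% | 7.0 / 7.0 | 1.0 |
| 10% / 10% | 90% / 60% | 9% / 6% | 7.0 / 4.6 | 1.5 |
| 10% / 10% | 60% / 30% | 6% / 3% | 4.6 / 2.3 | 2.0 |
| 10% / 10% | 90% / 30% | 9% / 3% | 7.0 / 2.3 | 3.0 |
| 10% / 20% | 90% / 45% | 9% / 9% | 7.0 / 7.0 | 1.0 |

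With a true risk of 5% or 20% in both arms the ratios are unchanged. The last row shows the reverse problem: twice the true risk on the wait list, recorded as no difference. If course members were instead reluctant to report to those running the course, s1 could fall below s0. Swapping the second row's capture rates gives 60/90 = 0.67. Each ratio restates its assumed inputs, so the table shows what is possible and does not estimate a bias.

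**The case against.** The other side has several good points.

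- **No harm comparison is planned.** The aims, the data analysis section and the outcome list contain none. A reader might infer that the trial's harm comparison is biased. The article does not support that, because no such comparison is stated. What stands is narrower: counts are to be registered in both arms, and if they are shown side by side they would be open to this bias.
- **Worsening is measured alike in both arms.** A reader might infer that deterioration on the wait list goes unseen. That is too broad. Perceived stress and mental health are collected in both arms at the same three times, a reliable change index is planned, and absenteeism is recorded for all. The gap is limited to events outside those measures or between assessments (the stress scale looks back one month), and to timely detection, since no review of scores for safety is described.
- **The trainer's role is modest.** A reader might infer that the trainer is instructed to watch for problems, or that course members must take problems to the trainer. Neither is stated. The text covers only what happens if the trainer notices something, and participants can go to the researchers or the psychologist directly.
- **The article may be condensed.** A report can also be an answer to a question, and the full protocol might contain a solicited item. Table 1 is weak evidence against this, as it also omits attendance, which is recorded. This limits confidence. It does not remove the point, because the article does state a method, and that method turns on the participant's report.
- **Low expected risk.** The Ethics Committee agreed that there was no risk of physical or mental harm, which can justify light monitoring. It bears on how much to ask. It does not justify collecting events unequally when the same section sets up registration for both arms.

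**Conclusion.** The point holds in a limited form. The stated rule is triggered by participants' reports, and only the MBSR arm has nine trainer meetings, trainer-advised referral and follow-up of non-attenders. Adverse-event counts by arm would therefore be prone to ascertainment bias, and events outside the stress and mental-health scales or between assessments are less likely to be recorded on the wait list.

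The size and direction cannot be fixed from the documents. With equal true risk, the assumed range of higher capture under MBSR gives apparent ratios of 1.5 to 3.0. Other assumptions give a ratio below 1 or hide a real difference. Nothing here affects the primary outcome, the sample size or any stated analysis.

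The conclusion assumes that the full protocol holds no solicited adverse-event procedure beyond what the article describes. If it does, the remedy is a sentence saying so. Otherwise this is a worthwhile, inexpensive improvement to safety capture.

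**What to change.** 1. Add one identical short adverse-event item to the remaining November and March questionnaires in both arms. It would ask about any new or worsened psychological or physical complaint, or contact with a care provider, since the last questionnaire (yes/no plus free text).
2. Base any between-arm description of harms on that item, for the cohorts that received it.
3. List spontaneous and trainer-noted events separately, by source, and mark earlier cohorts as spontaneous-only.

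**Cost.** One or two items in questionnaires already sent through the data-capture system, and a short amendment. Questionnaires become slightly longer and more minor events are recorded.

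**Reach.** The article is dated 23-11-2020. By Table 1, cohort 1 had finished its March 2020 follow-up and cohort 2's post-test fell in that same month. The item could fully cover cohort 3 (November 2021 and March 2022) and the March 2021 assessment of cohort 2. Cohort sizes are not given. If they were equal, full coverage would be about 155/3 ≈ 52 teachers, or 26 per arm, so the solicited data would be descriptive and cover only part of the sample.
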